### Sample size calculation

Based on the figures found in two studies on large uteri (Daraï et al., 2001; Hwang et al., 2002) and Baekelandt’s study of hysterectomies (Baekelandt et al., 2019), for an alpha risk of 5% and a power of 90%, a superiority study with an expected complication rate of 37% with laparoscopy and 15% with the vaginal route (i.e. an RR of 0.5 and therefore a relative reduction in risk of 50%) will need to include 119 patients per group, i.e. 236 in total. In order to compensate for possible loss of sight, 248 patients will be included.

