### Study design

An information brochure on the study will be given to all patients who meet the inclusion criteria of the study at the preoperative consultation. An evaluation of pain by EVA scale will be carried out during this consultation.

After obtaining the patient’s consent on the day of the operation, the allocation between the two groups will be done by randomisation. This randomisation will be stratified on the centre and uterine volume (280-500g; > 500g). The randomisation list will be a randomised computer list established before the beginning of the study. It will be balanced by blocks of variable size and centralised via the Ennov Clinical web platform.

Two groups of patients will be constituted: a “laparoscopic approach” group and a “vNOTES” group. Patients will not know their group of assignment.

All hysterectomies will be performed by vNOTES-trained surgeons (20 procedures performed) who will follow the standard operating procedure. In women assigned to the experimental arm, the surgeon will perform a hysterectomy with the vNOTES medical device. In the women assigned to the control arm, the surgeon will perform a laparoscopic hysterectomy.

A questionnaire assessing visual comfort, feeling of safety and satisfaction on Lickert scales will be completed immediately after surgery by the operator and the operating assistant.

The care provided by the anesthetists and nurses will be standardised and similar in both groups. To limit bias, in all cases the patient will have abdominal dressings as if it underwent a laparoscopy.

Once returned to the ward, all participants will be assessed every 2 hours and discharged home when the patient’s condition allows(Chung score ≥ 9/10).

Telephone interviews by the department CRA, blinded to the allocation group will be conducted daily for the first week to assess postoperative pain.

A follow-up visit by an independent adjudication committee, blinded to the allocated group will be performed 6 weeks postoperatively or earlier if a complication brings a patient to consult.

Finally, a telephone call will be made at 3 months to evaluate the sexual impact by a questionnaire (PISQ12 with a score ranging from 0 to 48) (Table I).

**Table I t001:** Conduct of the study.

Visits	V1	V2	V3	V4	V5	V6
Title of the visit	Pre-operative selection visit	Day of the intervention	Immediate post-operative follow-up	Telephone follow-up D1-D7	Post-operative visit at 6 weeks	Questionnaire at 3 months
Information	X					

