### Outcomes

The primary outcome is a composite endpoint including the occurrence of intraoperative and postoperative complications within 6 weeks of surgery. Intraoperative complications will be defined as injury to surrounding organs (bladder, ureters, rectum, colon, small intestine) or bleeding requiring immediate resumption, intraoperative transfusion and/or decreasing the patient’s haemoglobin by more than 2 points compared to the last known pre-operative blood test. Postoperative complications will be defined according to the Clavien-Dindo classification.

Regarding secondary outcomes, the need for conversion during surgery will be collected.

Post-operative pain at day 0 will be evaluated by the maximum daily pain felt on arrival in ambulatory surgery and at hour 3 after return from the block. Short-term postoperative pain during the first week after surgery will be measured by a numerical scale (0 to 10), determined on a daily telephone call. The consumption of analgesics other than those planned in the study in the immediate postoperative period and within 7 days will also be recorded. The duration of postoperative reflex ileus will be measured between the day of the operation and the resumption of a transit (appearance of the first gas) in hours. The duration of the operation from the incision to the end of the closure (in minutes). The duration of hospitalisation will be evaluated in days and the possibility of returning home by the time in hours between the surgical incision and the achievement of a Chung≥ score of 9/10. Sexual disorders: sexual life will be assessed by the difference in the specific validated score (self-questionnaire) (PISQ12 with a score ranging from 0 to 48) between the inclusion date and 3 months after surgery for sexually active women. The visual comfort, satisfaction and feeling of safety of the surgeon and the operating assistant will be evaluated via a Likert scale.

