### Statistical analysis

The included population will described globally and by group (vNOTES vs laparoscopic approach). The main analysis will be performed according to the intention-to-treat principle. The frequency of patients presenting with at least one complication will be estimated in each group, as well as the 95% confidence interval of this frequency. The effect of the surgical strategy will be estimated by the relative risk and the 95% confidence interval. The resulting p-value of Fisher’s exact test will also be given. As the secondary objectives are exploratory, no statistical test will be performed (i.e. no p-value will be estimated), according to the new NEJM recommendations.

For the qualitative secondary endpoints, the relative risk and its confidence interval will be given. For quantitative endpoints, differences in means will be calculated, as well as their 95% confidence intervals.

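### Preoperative pain is to be rated but is missing from Table I and the data list, and the pain comparison has no stated use of it or of the stratification factors

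*Protocol article*

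**What the plan says.** All references are to the protocol article.

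- **Study design** places a pain rating at the preoperative consultation: "An evaluation of pain by EVA scale will be carried out during this consultation". The same section stratifies the randomisation on centre and on uterine volume in two classes.
- **Outcomes** defines pain on day 0 (on arrival in ambulatory surgery and at hour 3) and then daily for a week: "Short-term postoperative pain during the first week after surgery will be measured by a numerical scale (0 to 10"). Both are postoperative values. By contrast, the PISQ12 outcome in the same section is defined as a difference from its value at inclusion.
- **Table I** has one pain row, for postoperative assessment, ticked at V3 and V4. Nothing on pain is ticked at V1.
- **Data collection** names postoperative pain and use of analgesics, but not preoperative pain.
- **Statistical analysis** has one rule for all continuous secondary outcomes: "For quantitative endpoints, differences in means will be calculated, as well as their 95% confidence intervals". Secondary objectives are called exploratory and get no p-values.

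**The concern.** There are two linked problems.

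First, the article disagrees with itself on whether preoperative pain is trial data. Study design has it rated, while the visit table and the data list leave it out. A site working from the table could skip the rating, and a baseline not recorded before surgery cannot be recovered.

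Second, even if the score is recorded, the article gives it no use. The stated estimator is a difference in means, and neither the baseline score nor the stratification factors enter it. The Discussion names less postoperative pain among the benefits sought for patients. Because secondary outcomes carry no p-values, the estimate and its interval are the whole pain result. A narrower interval at almost no cost is therefore worth having. What is at stake is interval width for an exploratory outcome, not the primary result or the sample size.

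**Working it through.** **No planned figure to reproduce.** The article gives no standard deviation, correlation, precision target or power for pain. The only sample size is for complications, and it serves here just to set the scale. The text reads "will need to include 119 patients per group, i.e. 236 in total". Since 2 × 119 = 238, I use 236 / 2 = 118 per arm. Using 119 leaves the half-width below at 0.51.

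**Step 1: the passages side by side.**

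| Section | Preoperative pain | Postoperative pain |
|---|---|---|
| Study design | rated at the consultation | daily calls in week 1 |
| Table I | absent | V3 and V4 |
| Data collection | absent | listed |
| Outcomes | absent | day 0 and week 1 |
| Statistical analysis | no stated use | difference in means, 95% CI |

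**Step 2: gain from baseline adjustment.** Let r be the within-arm correlation between preoperative and postoperative pain. Relative to the crude difference in means, the ANCOVA estimate has variance 1 − r² and interval width √(1 − r²). The crude analysis would need 236 / (1 − r²) women to match it. The last column assumes an SD of 2 points on the 0–10 scale. Its crude half-width is 1.96 × 2 × √(2/118) = 0.51, which is then multiplied by √(1 − r²).

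| Assumed r | √(1 − r²) | Interval narrower by about | Equivalent crude N | Half-width, SD 2 |
|---|---|---|---|---|
| 0.1 | 0.995 | 0.5% | 238 | 0.51 |
| 0.2 | 0.980 | 2% | 246 | 0.50 |
| 0.3 | 0.954 | 5% | 259 | 0.49 |
| 0.4 | 0.917 | 8% | 281 | 0.47 |
| 0.5 | 0.866 | 13% | 315 | 0.44 |

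The SD is also an assumption. With SD 1.5 the crude half-width is 0.38, falling to 0.33 at r = 0.5. With SD 3 it is 0.77, falling to 0.66. The percentage narrowing depends on r alone.

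**Step 3: price of adjusting.** Estimating one slope costs roughly 1/N of the variance: 1/236 = 0.4%, or about 0.2% of interval width. Centre and volume stratum are roughly balanced between arms by the stratified allocation, so adding them costs almost nothing. If they predict pain, a crude interval that ignores them is wider than it need be. The article gives no basis for sizing that part.

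**Step 4: why not a change score.** With equal SDs before and after, the variance of a change score relative to the crude difference is 2(1 − r). That is 1.4 at r = 0.3 and 1.0 at r = 0.5, so below r = 0.5 a change score is less precise than ignoring the baseline. Covariate adjustment does not have this drawback.

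**The case against.** The strongest reply is that a difference in means is an effect measure, and ANCOVA or a mixed model also yields one. The sentence in Statistical analysis does not rule out adjustment. Covariates for exploratory outcomes are often left to a statistical analysis plan, and this article condenses a longer protocol. That stands as a limit on the claim. A reader might infer that the plan commits to unadjusted comparisons, to seven separate daily intervals, or to each day's respondents only. The article states none of these. Its text supports only that one estimator is fixed for all continuous outcomes, with no covariate or model named.

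The second reply is that the effect is small. Baseline pain reflects uterine disease, while the outcome is acute surgical pain under standardised care, so a low correlation is plausible. At r = 0.2 or below the gain is 2% of width or less and would hardly change a conclusion. This also stands.

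Third, a reader might infer that chance imbalance in baseline pain makes the crude result wrong. It does not: the crude estimate is unbiased under randomisation, and its interval already allows for such imbalance.

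Finally, it is tempting to say that the baseline score is already in hand for every woman. The article does not establish this. Table I and Data collection omit it, and the rating belongs to the V1 consultation whereas consent is at V2. This leaves open whether the score will be available as trial data. It qualifies the analysis point, but makes the reconciliation more pressing.

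**Conclusion.** The point holds as an internal inconsistency plus a nearly free improvement. The inconsistency rests on the text alone: preoperative pain is planned in Study design but absent from Table I and Data collection. The improvement is to give that score and the stratification factors a stated role in the pain comparison, which they now lack.

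The benefit is precision only. It runs from about 0.5% of interval width at r = 0.1 to about 13% at r = 0.5. The correlation is assumed throughout, and nothing in the article shows where in that range the trial would fall. The calculation also assumes 1:1 allocation and a roughly linear relation between baseline and outcome. The different names of the two scales (EVA before surgery, a numerical scale after) do not prevent use of the baseline as a covariate. The primary analysis and the sample size are unaffected.

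**What to change.** 1. Reconcile the sections: add the preoperative pain score at V1 to Table I and to Data collection. This comes first, because the adjustment depends on it and the score cannot be collected afterwards.
2. Amend Statistical analysis so that pain differences in means are estimated with baseline pain, centre and uterine volume stratum as covariates. Use ANCOVA for day 0, and ANCOVA or a repeated-measures model for days 1 to 7. Report the adjusted mean difference with its 95% confidence interval.
3. Enter baseline pain as a covariate rather than analysing change from baseline.
4. Optional: report a single week-1 summary in place of daily differences. This is a choice of what to estimate, and the correction does not depend on it.

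The cost is one table row, one entry in the data list and a sentence or two of analysis text. If the preoperative rating is carried out as Study design describes, there is no added measurement. If it is not being recorded, the cost is one pain rating per woman.

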## Discussion

The available data from randomised controlled trials are insufficient to recommend the use of vNOTES for a hysterectomy in this case large volume uteri .

The first evaluations of vNOTES are encouraging and suggest a new era for pelvic surgery: less postoperative pain, fewer complications and facilitation of ambulatory care. Also the videoscopic assistance of the vNOTES is a pedagogical tool for the vaginal approach because the field of vision is no longer limited to the operator alone. Our study would be the first multicentric and academic study on vNOTES to focus specifically on large volume uteri , which are recognised as more difficult operations and prone to postoperative complications.

The expected benefits of this study are severalfold. For public health, the main objective is to reduce the length of hospitaliation. From the point of view of the patients, this study seeks a reduction in the length of hospitalisation, postoperative complications and postoperative pain. For the surgeon, it would improve visual comfort during surgery and the feeling of safety, as well as being an educational aid for teaching interns. The latter could effectively gain in visual comfort during surgery.

We hope that this large-scale, multicentric, randomised trial will lead to a better understanding of the approach to large uteri . Each year, several thousands of women undergo a hysterectomy in France; this study will support the evidence for optimal surgical care and better patient outcomes.
